### Criteria

The inclusion and exclusion criteria are reported in Textbox 1.

Inclusion and exclusion criteria.
**Inclusion criteria**
Patients with upper respiratory tract infection (URTI) who are administeredPudilan Xiaoyanoral liquid; the diagnostic criteria for URTI are based on the disease code J06.900 of theInternational Classification of Diseases, 11th RevisionAged between 18 and 80 years
**Exclusion criteria**
Lactating women, pregnant women, those planning to become pregnant, patients with psychiatric conditions, and others

### Instructions for Taking Medicine

In the respiratory and emergency departments of the hospitals under surveillance, the medication of PDL is observed for those aged 18-80 years who strictly follow the prescribing instructions: taking PDL 10 mL at a time, 3 times a day. During hospitalization, the patient must take PDL at least once. The patients will be visited and checked before and after taking the medicine.

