**Methods:**

The study is a prospective, observational, multicenter, hospital-based surveillance study. A total of 17 hospitals from China are involved. The study is expected to enroll a large sample of 10,000 patients aged between 18 and 80 years with upper respiratory tract infection who were prescribed PDL. The patients’ data, including demographics, medical history, diagnostic information, medication details, adverse events, and laboratory test results, will be monitored. The occurrence of ADRs will be recorded. The primary outcome is the incidence of ADR. Secondary outcomes are the ratio of patients whose body temperature return to the normal range (cases of body temperature normalization and the duration for achieving normal body temperature within a 3-day period will be documented) and changes in liver and kidney function (occurrence of drug-induced liver injury and acute kidney injury). Descriptive analyses will be performed for the primary and secondary outcomes. A cohort, nested, case-control study design will be used. If one patient has an ADR, then 4 patients without ADRs will be matched as the control group according to gender, age within 5 years, drug batch, and other factors, at a ratio of 1∶4 to compare the symptoms related to ADRs. The differences of ADR incidence among the possible influencing factors will be compared separately to find the factors with large differences. Then, synthetic minority oversampling technique and group least absolute shrinkage and selection operator methods will be used to identify factors influencing the occurrence of ADRs. Finally, propensity scoring methods will be used to control for confounding variables. The progress of each subcenter will be closely monitored, and the incidence of ADR will be systematically calculated. Furthermore, the characteristics and influencing factors of ADR will be analyzed, along with an investigation into its geographical distribution.

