Monitoring the unintended effects of a drug (pharmacovigilance or drug safety) is crucial due to limited knowledge of rare or late-stage side effects upon market release of new drugs [13,14]. In recent years, numerous related studies have reported the clinical efficacy of PDL; however, there were few independent safety studies on it, most of which were small scale and exhibited significant variations in reported safety outcomes across different studies [15-18], resulting in inadequate understanding of its safety monitoring. In summary, published safety data on adverse effects of PDL therapy were insufficient, thereby impeding the use of standardized recommendations that are necessary for ensuring drug safety.

Although Chinese patent medicine generally exhibits a low incidence of adverse reactions, the evidence pyramid classification derived from effectiveness evaluations primarily considers randomized controlled trials as high-level evidence. However, this classification standard may not fully meet the evidence requirements for postmarketing drug safety evaluation due to limitations such as short intervention courses or small sample sizes, often resulting in an inability to detect ADRs and differences between groups. For the above reasons, this study intends to adopt a large-scale, multicenter, long-term, noninterventional, observational study design to comprehensively analyze and report on the occurrence of adverse events (AEs) [19].

The mechanism of kidney metabolism and excretion of various drugs and toxins is an important cause of drug nephrotoxicity [20], while studies have shown that most of the AEs related to the urinary system were from treatment with PDL [21]. It can be seen that the kidney damage caused by PDL needs further investigation. As hepatic function plays an essential role in drug metabolism [22], clinical studies are necessary to determine the characteristics of PDL-related hepatotoxicity. Additionally, the influencing factors of other PDL-related adverse reactions are still unclear and may be related to the inherent characteristics of the drug itself, improper usage and dosage, improper combination, repeated administration, or use without indications, which need further investigation and study. Furthermore, a comprehensive study regarding the adverse effects associated with PDL use in patients is imperative to optimize the risk-benefit ratio and alleviate strain on limited health care resources.

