### Monitoring Time and Follow-Up

Patients are monitored throughout the medication period in the hospital. The treatment duration of PDL for URTI ranges from 3 to 14 days. This study will include a follow-up period of 7 days after the completion of observation treatment [26], aiming to assess the drug’s long-term efficacy and observe any delayed ADRs. The follow-up will be conducted either through face-to-face meetings or via telephone communication. We will use systematic methods and reminders to schedule appointments with patients.

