### Outcome Measures

#### Primary Outcome Measure: Incidence of ADRs

The incidence of ADRs is the primary outcome measure, and we will identify factors that contributed to the occurrence of ADRs. The incidence of ADR will be primarily categorized in accordance with the criteria proposed by the Committee of International Organization of Medical Sciences: very common (≥10%), common (1%-10%, including 1%), occasional (0.1%-1%, including 0.1%), rare (0.01%-0.1%, including 0.01%), and very rare (<0.01%) [28], as well as according to the classification of ADR symptoms by the World Health Organization (WHO) [29]. The WHO classification of organs and systems involved in ADRs will also be referenced [30]. The incidence characteristics and regional distribution will be subsequently analyzed, while concurrently investigating the influencing factors (Table 2).

**Table 2 table2:** Centralized monitoring results of Pudilan Xiaoyan oral liquid in the registered hospitals.

Monitoring result	Description
Categorization	The ADR^a^ was categorized based on general, novel, and severe classifications The classification was based on the organs and systems affected by the ADR The symptoms of the ADR were classified
ADR incidence	The specific event features of each ADR included the incidence rates of various categories and whether they are infrequent or exceptionally rare
Pedogenic properties	Occurrence characteristics of ADRs specific to each category
Geographical distribution	The distribution of ADRs is primarily observed in North China, Central China, South China Each region exhibits distinct characteristics of ADRs
Influencing factors	Days of medication, age, drug combination, etc

^a^ADR: adverse drug reaction.

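### Describing the observed patients as strict followers of the labelled regimen does not fit the eligibility text and, if applied as a filter, could distort the primary ADR incidence

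*Protocol article*

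**What the plan says.** The protocol article describes the patients under surveillance in several places.

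- **Abstract, Methods:** the study enrols "patients aged between 18 and 80 years with upper respiratory tract infection who were prescribed PDL". There is no adherence condition.
- **Textbox 1, inclusion criteria:** the entry begins "Patients with upper respiratory tract infection (URTI) who are" and continues with administration of PDL; the age range is 18 to 80. The exclusion criteria listed do not mention adherence.
- **Instructions for Taking Medicine:** PDL use is observed in those "who strictly follow the prescribing instructions: taking PDL 10 mL at a time, 3 times a day". The next sentence reads "During hospitalization, the patient must take PDL at least once".
- **Monitoring Time and Follow-Up:** "The treatment duration of PDL for URTI ranges from 3 to 14 days", and "This study will include a follow-up period of 7 days after the completion of observation treatment".
- **Interpretation of ADR Causality:** dechallenge is one of five causality criteria, and the times of ADR onset, of intervention and of ADR termination are recorded.
- **Introduction:** possible causes of ADRs that need study include "improper usage and dosage, improper combination, repeated administration, or use without indications".
- **Outcome Measures:** "The incidence of ADRs is the primary outcome measure". Table 2 lists days of medication among the influencing factors.

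**The concern.** Whether a patient strictly followed a course of 3 to 14 days can be known only during or after that course. It is not a baseline characteristic. It can also be changed by the outcome: someone who reacts to PDL may skip doses or stop. A patient who takes one dose, reacts and stops is eligible under the Abstract, Textbox 1 and the one-dose minimum, but is not a strict follower of a regimen of three doses a day.

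If a site applies the sentence literally, that patient leaves both numerator and denominator of the primary outcome. The ADRs most likely to interrupt treatment would then be the ones most likely to be missed, in a study whose purpose is to measure real-world safety. With 17 hospitals, sites could also read the sentence differently, which would blur the planned regional comparison.

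A second consequence concerns the influencing factors. A population held to one amount and one frequency offers no variation in those two aspects of use, so it could not inform the question about improper usage and dosage that the Introduction raises.

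**Working it through.** **1. The plan's own figure.** The article gives no figure for adherence. Its only sample-size calculation is the rule of three: 3/p at p = 1/1000 gives 3000, and the exact form ln(0.05)/ln(1 − 0.001) gives 2994. The stated 3000 is reproduced, and this point does not affect it or the extension to 10,000.

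**2. Text comparison.**

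| Place in the article | Who counts, as written | Patient who stops after an ADR |
|---|---|---|
| Abstract | prescribed PDL | in |
| Textbox 1 | administered PDL | in |
| Instructions, second sentence | one dose or more | in |
| Causality section | dechallenge is assessed | must be in, to be graded on this criterion |
| Instructions, first sentence | strict followers of the regimen | out, if read as a filter |

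**3. Effect if the sentence is used as a filter.** Inputs:

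- p = true ADR incidence (assumed)
- a = share of ADR patients removed for departing from the regimen (assumed)
- b = the same share among ADR-free patients (assumed)

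Observed incidence = p(1−a) / [p(1−a) + (1−p)(1−b)]

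For small p, observed/true ≈ (1−a)/(1−b).

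Worked case with 10,000 enrolled, p = 1%, a = 50%, b = 10%:

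- 100 patients have an ADR, of whom 50 are kept.
- 9,900 have none, of whom 8,910 are kept.
- Observed incidence = 50/8,960 = 0.56%.

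| a (ADR) | b (no ADR) | Observed at p = 1% | Observed/true |
|---|---|---|---|
| 10% | 10% | 1.00% | 1.00 |
| 30% | 10% | 0.78% | 0.78 |
| 50% | 10% | 0.56% | 0.56 |
| 10% | 20% | 1.12% | 1.12 |

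The ratio hardly depends on p: at a = 50%, b = 10% it is 0.556 for p = 0.1% and 0.561 for p = 2%.

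**4. Direction.** The ratio is below 1 only if a > b. It equals 1 if a = b and exceeds 1 if a < b.

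**5. Frequency category.** At a = 50%, b = 10%, a true 1% falls to 0.56% and crosses the article's cut between common and occasional. A true 2% becomes 1.12% and stays common; a true 0.5% becomes 0.28% and stays occasional. A change of category therefore depends on how close the true value lies to a cut.

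**The case against.** The strongest reply is that the sentence is not an eligibility rule. It stands under a heading about taking the medicine, while eligibility is set in Textbox 1, which has no adherence criterion. It may mean only that PDL is prescribed at the labelled regimen. Nothing in the article says that a patient who skips or stops doses is withdrawn or removed from the denominator. The monitoring section has all patients complete CRF A, with CRF B added when an ADR or AE occurs. The use of dechallenge and of days of medication suggests that patients who stop are expected to remain under observation. This stands: the article does not establish that such patients are lost.

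Two further parts of the reply also stand.

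- A one-dose minimum for entry can coexist with a labelled regimen. That pair is unreconciled rather than strictly contradictory.
- The Introduction calls URTI self-limiting, so ADR-free patients may also stop early. A reader might infer that the primary incidence is biased downward as a matter of course; that requires both that the filter is applied and that a exceeds b.

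A reader might also infer that no question about usage could be answered. That goes too far: days of medication, age and drug combination can vary among patients on the labelled regimen. Only amount and frequency would be fixed.

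What the reply does not remove is the sentence itself. It repeats the age range, names the departments and states in whom PDL use is observed, so a site can reasonably read it as defining the monitored population. This is a conflict within the article's own text, not detail left to an analysis plan.

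**Conclusion.** The wording needs to be reconciled. As written, one sentence ties observation to behaviour after exposure that an ADR can change, and it does not fit the Abstract, Textbox 1, the one-dose minimum, the use of dechallenge or the stated interest in improper usage.

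Applied as a filter, it would understate the primary incidence whenever ADR patients depart from the regimen more often than others. That direction is plausible, since a reaction is a reason to stop, but the documents do not show it. Under the assumed shares the observed incidence runs from 0.56 to 1.12 times the true one. If every patient with at least one dose is counted, this source of bias is absent. A shift from common to occasional is possible but should not be presented as the expected result, because it needs a true incidence near 1%.

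**What to change.** - Reconcile the Instructions for Taking Medicine section with the Abstract, Textbox 1, the causality section and the Introduction, leaving every dosing instruction as it is.
- State that the primary ADR incidence counts all enrolled URTI patients who took at least one dose, whatever their later adherence.
- Use actual use (amount, frequency and days) as a candidate influencing factor. The Abstract already lists medication details among the monitored data, so check first whether CRF A captures these.
- Report any strictly adherent subset only as a sensitivity analysis.
- Because enrolment has run since July 2019, ask the sites whether anyone was left out on this ground.

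The cost is minor: a wording change, possibly some extra data entry on actual use, and a query to the 17 hospitals. Treatment and the planned 10,000 cases are unaffected.

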### Monitoring Content and Data Administration

#### Monitoring Patient Data, Demographic Information, Diagnosis, Complications, and Medication Information

A collaborative monitoring approach involving doctors, nurses, and pharmacists will be used in this study. They will receive relevant training in surveillance knowledge.

#### Basic Information Form for Administering PDL

The researchers will record the AE information collected during the study period into the safety monitoring case report form (CRF). All patients will be required to complete CRF A (PDL basic information form). If the monitored patient experiences an ADR or AE during the medication period, the monitor will need to fill out CRF B. We will check the monitoring data; enter, encode, standardize, and clean the data; and then conduct a third-party data inspection. Any discrepancies in the data will be addressed by two data administrators who will resolve them after independently verifying the original CRFs.

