### Interpretation of ADR Causality

In this study, AEs, ADRs, and serious ADRs will be judged according to the *Administrative Measures on Reporting and Monitoring for Adverse Drug Reaction* issued by the Ministry of Health in 2011 [27]. The evaluation of ADRs follows a 3-level decision-making process, comprising initial reporting by clinical practitioners, assessment by the Expert Committee for ADR Monitoring at the surveillance center, and final determination by panel of senior domestic experts. Based on established assessment criteria, the causal relationship between AEs and PDL will be evaluated according to five key parameters: (1) temporal plausibility, (2) consistency with known mechanisms of action or established adverse reaction profiles, (3) positive dechallenge response, (4) positive rechallenge response, and (5) exclusion of alternative explanations. The correlation between AE and PDL will be divided into six grades: positive, probable, possible, possibly unrelated, to be evaluated, and unable to be evaluated. Those judged to be the first three grades will be classified as ADRs, those judged to be “possibly unrelated” will be classified as AEs, and those judged as “to be evaluated” or “unable to be evaluated” should be rejudged in combination with the original monitoring data. We will conduct thorough evaluations to ultimately confirm the incidence of ADRs associated with PDL. This approach helps to minimize potential biases associated with patient self-reporting and variations in medical practices across different centers. The occurrence characteristics and processes of ADRs will be meticulously documented, with particular emphasis on the timing of ADR onset, the implementation time of intervention measures for ADRs, and the termination time of ADRs.

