### Quality Control of ADRs

Each monitoring subcenter will formulate the first-level, quality-control rules and quality-control list according to the content of the monitoring program. The information system of each monitoring unit will be reviewed to ensure that the clinical study data are authentic and traceable. The implementation of the study will adhere to the research protocol and standard operating procedures in order to ensure the authenticity and reliability of the research data. The data collected are presented in Table 1.

**Table 1 table1:** Basic information form for administering Pudilan Xiaoyan oral liquid^a^.

Basic information	Before taking the medicine	After taking the medicine		
		7 days	14 days	21 days
Age	✓			
Sex	✓			
Smoking history	✓			
Occupation	✓			
Expense category^b^	✓			
Pathways to admission	✓			
Drinking alcohol	✓			
Western medicine diagnosis	✓			
Traditional Chinese medicine diagnosis	✓			
Past medical history	✓			
Personal history of allergies	✓			
Allergic manifestation	✓			
Previous other adverse drug reactions or events	✓			
Main drug combination: Western medicine, antibiotics, antipyretic analgesia, proprietary Chinese medicine, or other drugs		✓	✓	✓
Blood routine before and after treatment, white blood cell count, granulocyte, routine urine examination, liver function, renal function, ECG^c^ (test sheet within 30 days before treatment), C-reaction protein, influenza virus detection, pathogen detection, and other tests	✓	✓	✓	✓
Adverse reaction occurrence (yes or no)		✓	✓	✓

^a^Patients are visited and examined before and after taking the medication.

^b^Expense category refers to the classification of expenses, such as out-of-pocket (self-funded) costs, expenses covered by medical insurance, and other payment types. It helps in understanding how different types of expenses are categorized based on their funding source or payment method.

^c^ECG: electrocardiogram.

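### The trigger for the event form (CRF B) stops at the end of medication, short of the 7-day follow-up meant to catch delayed ADRs, so post-dose ADRs risk incomplete documentation and under-counting

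*Protocol article*

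**What the plan says.** All references are to the protocol article.

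- **Basic Information Form for Administering PDL.** The section opens with a general statement: "The researchers will record the AE information collected during the study period into the safety monitoring case report form (CRF"). It then gives every patient CRF A and states when the event form is due: "If the monitored patient experiences an ADR or AE during the medication period, the monitor will need to fill out CRF B".
- **Monitoring Time and Follow-Up.** Two periods are distinguished. The first is treatment: "Patients are monitored throughout the medication period in the hospital", and "The treatment duration of PDL for URTI ranges from 3 to 14 days". The second comes after it: "This study will include a follow-up period of 7 days after the completion of observation treatment", with the purpose given as "aiming to assess the drug’s long-term efficacy and observe any delayed ADRs". Contact in the second period may be by telephone.
- **Quality Control of ADRs, Table 1.** The reaction item on the basic form is "Adverse reaction occurrence (yes or no"), ticked at 7, 14 and 21 days. Concomitant drugs and laboratory tests are ticked at the same visits.
- **Interpretation of ADR Causality.** Events are judged on five parameters, among them timing, dechallenge and the exclusion of other causes. ADRs are to be documented "with particular emphasis on the timing of ADR onset, the implementation time of intervention measures for ADRs, and the termination time of ADRs". Only the top three of six grades count as ADRs.
- **Change in Renal Function.** A closing line gives all four outcomes a 7-day time frame and does not say when it starts.

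**The concern.** The follow-up exists partly to find ADRs that appear after treatment. The form that would describe such an event is required only for events during treatment. A site that follows the CRF B sentence to the letter would answer yes at a follow-up contact and complete no event form.

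The primary outcome is the incidence of ADRs, and an event enters it only after causality grading. An event recorded without onset date, course after stopping PDL, or end date is harder to place in one of the three qualifying grades. The likely direction of any bias is therefore downward. There is a second effect in the nested case-control analysis (Statistical Analysis): a patient whose delayed reaction is not confirmed could be drawn as one of the four matched controls without ADRs, which would blur the comparison of risk factors.

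**Working it through.** **1. The windows side by side.**

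| Item | Period covered | Section |
|---|---|---|
| AE recording in general | study period | Basic Information Form |
| CRF B required | medication period | Basic Information Form |
| Follow-up for delayed ADRs | 7 days after treatment | Monitoring Time and Follow-Up |
| Yes/no reaction item, concomitant drugs, laboratory tests | days 7, 14, 21 | Table 1 |
| Onset, intervention and termination times of ADRs | no limit stated | Interpretation of ADR Causality |
| All four outcomes | 7 days, start not given | Change in Renal Function |

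The follow-up section separates treatment from what comes after it, so the medication period cannot fairly be read to include follow-up. The CRF B row is therefore narrower than the first, third and fifth rows.

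**2. Does Table 1 reach the end of follow-up?** Longest course plus follow-up: 14 + 7 = 21 days. If days are counted from first dose, this agrees with the last column of Table 1. Contacts are thus planned for the post-dose period; what is missing is the instruction to complete the event form.

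**3. Days outside the trigger.** For a course of t days followed by 7 days, the share is 7/(t + 7).

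- t = 3: 7/10 = 70%
- t = 7: 7/14 = 50%
- t = 14: 7/21 = 33%

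If instead the 7-day outcome time frame governs and runs from the first dose (an assumption), the share is (7 − t)/7 for courses under 7 days: 4/7 = 57% for t = 3, and zero for courses of 7 to 14 days. The exposure depends on which window is meant.

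**4. What that could mean for incidence.** The documents do not say what share of ADRs begins after the last dose. As an illustration only, assume a share s between 5% and 50%, and that every such ADR is lost, which the documents do not state. Counted ADRs = 10,000 × true incidence × (1 − s).

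- True incidence 1.0% (100 ADRs): 95 to 50 counted, that is 0.95% to 0.50%.
- True incidence 0.10% (10 ADRs): 9.5 to 5 counted on average, that is 0.095% to 0.05%.

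These are upper limits on the loss for each assumed share, not estimates.

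**The case against.** The strongest reply is that the article provides for post-dose events in several other places.

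- The opening sentence on AE recording covers the study period, and the CRF B sentence does not say that the form is barred later.
- Table 1 is the basic form, where a screening item is what one would expect. It also collects concomitant drugs and laboratory tests to day 21. Post-dose laboratory abnormalities are therefore captured whether or not CRF B is completed.
- The causality section asks for ADR times without a period limit and starts from the practitioner's report. It sends ungradable events back to be rejudged against the original monitoring data.
- The content of CRF B, its completion instructions and the site procedures are not shown.

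Much of this stands. A reader might infer that delayed ADRs are never documented well enough to be judged and drop out of the primary incidence; no section says so, and no rule removes them from the numerator. A reader might also take 70% or 33% as the proportion of ADRs lost, but these are shares of calendar days. Nor is an abnormality found on day 7 of a short course necessarily post-medication: onset may precede detection, and Table 1 does not say whether its days run from first or last dose.

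The contradiction itself is not answered. The general sentence and the specific instruction sit in the same section and point different ways, so sites may follow either. The causality section states what detail is needed but names no form for it outside the CRF B trigger. Rejudgment may add little, because the Statistical Analysis section takes the paper form as the original record, and without CRF B that may be only the basic form.

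**Conclusion.** The point holds as an inconsistency that bears on the primary outcome. The CRF B trigger is narrower than the follow-up set up to observe delayed ADRs, and it conflicts with the section's own statement on study-period recording. Followed as written, post-dose ADRs risk incomplete documentation, harder causality grading and under-counting, and some affected patients could serve as controls.

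The direction of bias is probably downward. Its size cannot be derived from the documents: it depends on the share of ADRs with post-dose onset, on which of the two sentences sites follow, and on which window governs the outcome. Certain loss of these events is not supported. The conclusion rests on the article's wording alone; a wider trigger in the unseen full protocol or form instructions would reduce the matter to correcting the article.

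**What to change.** Amend the CRF B sentence so that the form is completed for every ADR or AE with onset or first detection from the first PDL dose to the end of the 7-day post-treatment follow-up. Say explicitly that this includes patients who stop PDL early and events reported by telephone. Reconcile this window with the 7-day time frame given for the outcomes and state that time frame's starting point, so that one window governs CRF B, causality assessment and the primary numerator.

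For patients already enrolled (the first was included in July 2019), complete CRF B from source records for every yes on the Table 1 reaction item that has no CRF B, where records allow. Do this before the primary analysis and before controls are selected.

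The cost is one sentence in the protocol and form instructions, plus some extra forms at contacts already planned. Retrospective completion will be imperfect, particularly for the earliest patients.
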